**Fig. 3 Fig3:**
[figure not shown]
Schema showing trial groups, activities, endpoints and trial timeline

### Intervention description {11a}

The intervention was initiated at the same time in all clusters across the trial area. The experimental intervention in this trial is the scheduling of PCV13 for infants resident in geographic clusters of villages with the first dose due at 6 weeks of age and a booster dose scheduled at 9 months of age. The standard intervention is the scheduling of PCV13 for infants with doses due at 6, 10, and 14 weeks of age. There are few data to indicate the period of time required for the dissipation of the population-level effects of a PCV schedule while transitioning to a new schedule. Data from PSP in rural Gambia suggest that, in the 2-year period following the introduction of PCV13, herd effects were developing as the incidence of PCV13 only serotype IPD in the 2–4 years age group had fallen from 50 per 10^5^ person-years in 2010/2011 to 20 in 2013, despite coverage of PCV13 in mid-2013 being only 10% in this age group [9]. At the time the intervention was initiated, the 1 + 1 schedule was implemented with catch-up of the booster dose for infants up to 9 months of age who had already received two or three doses of PCV, the rationale being that this would be the approach if countries were to transition from a 3 + 0 schedule to a 1 + 1 schedule, and not waste doses of PCV. Catch-up of the booster dose was implemented for 4 months and then ceased.

PCV13 vaccine is licenced in many countries and has been approved for use in The Gambia since 2011. The EPI procures the vaccine through global systems coordinated by UNICEF. This trial delivers PCV13 in collaboration with, and through the structures of the Gambian EPI, and under the operational conditions of the public health system. The EPI receives PCV13 into a central cold-storage facility. Vaccine is transported to the regional centres either by a specially designed EPI ‘cold van’ or by cold storage units carried by Regional Health Directorate (RHD) vehicles. The RHDs in URR and CRR are based in Basse and Bansang respectively. The URR RHD stores vaccine in solar refrigerators in Basse and the CRR RHD stores vaccine in a purpose-built ‘cold room’ in Bansang. From Basse and Bansang, small volumes of vaccine are distributed on a monthly basis to eight ‘base clinics’ in Basse, Gambisara, Demba Kunda, Fatoto, Koina, Sabi, Bansang, and Brikamaba. These base clinics carry small volumes of vaccine to each of the EPI clinics in the 68 different geographic locations involved in PVS. Solar vaccine refrigerators are used for storage at the base clinics. The trial uses the existing EPI procedures to monitor and record the vaccine accountability and cold chain documentation with daily logs.

Immunisation is undertaken at the 11 fixed health centres in the study area on one to two days each week. Mobile clinics in the 57 other sites are held once or twice per month. Given the frequency of EPI clinics, there is generally some delay in the time that vaccines are actually received. Administration of PCV13, and other antigens, by EPI staff will follow the schedule allocated for the particular geographic cluster (Table 1), apart from when a list of exceptions dictate that an infant receives the schedule of the other group and not the locally allocated schedule (Table 2). In 2016 coverage in the BHDSS of three doses of PCV at 12 months of age was 92% and coverage of one dose of measles vaccine was 82% with measles coverage of 92% by 18 months of age.

**Table 1 Tab1:** Vaccination schedule in the Pneumococcal Vaccine Schedules (PVS) trial

Age	1 + 1 schedule			3 + 0 schedule	
	PCV13	Other antigens		PCV13	Other antigens
At birth or soon after	No	BCG, OPV 0, Hep B		No	BCG, OPV 0, Hep B
6 weeks	PCV13	Penta 1, OPV 1, Rota 1		PCV13	Penta 1, OPV 1, Rota 1
10 weeks	No	Penta 2, OPV 2, Rota 2		PCV13	Penta 2, OPV 2, Rota 2
14 weeks	No	Penta 3, OPV 3		PCV13	Penta 3, OPV 3
Nine months	*PCV13	MR, YF, OPV 4		No	MR, YF, OPV 4
Twelve months	**	MenA, DTP booster		No	MenA, DTP booster
Eighteen months	**	MR, OPV5		No	MR, OPV 5

*For a 4-month period after the initiation of the intervention, infants allocated to 1 + 1 who had already received two or three doses received a dose of PCV13 at age 9 months

**PCV13 booster may be administered beyond the scheduled age if not given at age 9 months

**Table 2 Tab2:** Circumstances when infants will not receive the locally allocated schedule for PCV13

Locally allocated schedule	Reason not to receive locally allocated schedule
3 + 0	Infant resident in 1 + 1 cluster and visiting a 3 + 0 clinic Infant completed 1 + 1 schedule and migrated to 3 + 0 village
1 + 1	Infant resident in 3 + 0 cluster and visiting 1 + 1 clinic Infant completed 3 + 0 schedule and migrated to 1 + 1 village Declined or withdrawn consent Non-resident

### Criteria for discontinuing or modifying allocated interventions {11b}

Trial participants are discontinued from participation in the study if:
Any clinically significant adverse event, intercurrent illness, or other medical condition or situation occurs such that continued participation in the study would not be in the best interest of the participant.The parent or guardian so desires.

Participants who attend an EPI clinic outside their cluster and within the study area, but continue to reside in their original cluster, receive the trial schedule originally indicated on their infant welfare card and on the trial sticker. If participants migrate within the study area before completing their PCV schedule they continue to receive the trial schedule allocated in the cluster of their new residence (Table 2). Participants who migrate after completing their PCV schedule do not receive any further doses of PCV in the cluster of their new residence (Table 2). Parents in the 1 + 1 group are advised that if they migrate permanently out of the trial area they should attend the next available EPI clinic to complete the standard schedule for PCV. If an infant allocated to the 1 + 1 group visits an EPI clinic outside the study area the parent is instructed to request that their child receive the trial schedule indicated on the infant welfare card and study sticker. The study sticker includes free-call telephone numbers so that parents, or EPI staff outside the study area, may call for guidance. Infants resident in the alternative schedule clusters who decline consent are assigned to the national standard schedule.

### Strategies to improve adherence to interventions {11c}

Adherence to the trial vaccination schedules is facilitated by exclusion criteria including an intention to migrate out of the study area before 4 months of age. Migration out of the trial area is limited; on average, only 10 children per cluster per year migrate out of the area. Also, lists of infants allocated to the 3 + 0 group who have not completed three doses by the age of 5 months, and lists of infants allocated to the 1 + 1 group who have not received the booster dose by the age of 11 months, are generated every month to guide defaulter tracing at home visits throughout the study area.

### Relevant concomitant care permitted or prohibited during the trial {11d}

PCV13 has been co-administered with Measles-Mumps-Rubella [35] and Measles-Mumps-Rubella-Varicella [36] vaccines but the results of both these studies do not report investigations of potential interference between the vaccines. PCV10 (Synflorix®) has been co-administered with yellow fever vaccine in a study of an investigational GSK vaccine although investigations of potential interference between the vaccines have not been published. A different investigational PCV10 vaccine manufactured by the Serum Institute of India has been co-administered with yellow fever vaccine with non-inferior immune responses [37]. Studies of yellow fever vaccine co-administration with polysaccharide protein-conjugate quadrivalent meningococcal vaccine had not detected any adverse interaction [38]. The investigators are not aware of any data, or ongoing studies, that evaluate potential immune interference with the co-administration PCV13 and yellow fever vaccine. An accompanying paper describes the protocol for a related trial in which we are investigating the effect of co-administration of PCV13 and yellow fever vaccine.

### Provisions for post-trial care {30}

The trial may be stopped early if there is evidence that the risk of pneumococcal disease is greater in one compared to the other trial group. If the Data Monitoring Committee (DMC) recommends that the trial be stopped early, a joint meeting of the DMC, Trial Steering Committee (TSC) and Central Stakeholder Committee will make a recommendation to the Sponsor regarding post-trial procedures, including whether a dose of PCV be administered to children in a group found to have inferior PCV-induced protection. LSHTM carries clinical trial/non-negligent harm insurance and medical malpractice insurance applicable to this trial.

### Outcomes {12}

The outcomes in the trial and the timing of their measurement are shown in Fig. 3. The primary trial endpoint is:
NP carriage of VT pneumococci in children aged 2 weeks–59 months with clinical pneumonia presenting to health facilities in the study area (measured in year 4).

Secondary endpoints will be:
NP carriage of non-vaccine type (NVT) pneumococci in children aged 2 weeks–59 months with clinical pneumonia presenting to health facilities in the study area (measured in year 4).Population-based and age-stratified NP carriage prevalence of VT and NVT pneumococci (measured in years 2 and 4).NP carriage of VT and NVT pneumococci in infants presenting for the first dose of PCV aged 6–12 weeks (measured in year 4).Incidence of radiological pneumonia in children aged 2 weeks–59 months (safety endpoint).Incidence of clinical pneumonia in children aged 2 weeks–59 months (safety endpoint).Incidence of clinical pneumonia associated with NP carriage of VT and NVT pneumococci in children aged 2 weeks–59 months (safety endpoint).Incidence of serotype-specific IPD in children aged 2 weeks–59 months (safety endpoint).Incidence of hospitalisation in children aged 2 weeks–59 months (safety endpoint).Mortality rate in children aged 2 weeks–59 months (safety endpoint).

#### Justification of outcomes

Measuring the prevalence of VT pneumococcal carriage in children with pneumonia and in the community are effective methods to determine the population-level effect of PCV schedules on pneumococcal transmission. The primary endpoint relates to the important public health condition of clinical pneumonia in children and the associated VT pneumococcal carriage correlates with community-level transmission. This primary endpoint may be replicated in other settings that investigate the transition from a standard to alternative PCV schedule. The primary endpoint will be measured in Year 4 when the differential effects of the two schedules have stabilised [32–34]. To explore potential early impact of the alternative schedule, we will conduct a secondary exploratory measurement of VT carriage prevalence in children with clinical pneumonia in year 2, specifying a superiority hypothesis (Fig. 3).

Surveys of pneumococcal carriage in the community have little selection bias as all residents of all ages are included in the sampling frame. Compared to VT prevalence in children with clinical pneumonia, the community-level VT carriage measurement is less prone to information bias as participants do not need to meet the clinical pneumonia criteria to have a NP swab. Cross-sectional surveys are a quick and relatively inexpensive way to measure VT carriage in the study population and give a broad scope of the effects of the two PCV schedules in different age groups. The population survey of VT carriage in year 2 will allow an exploratory measurement of any immediate impact from the alternative PCV schedule. The year 2 survey will be completed in parallel with a survey of interpersonal contact patterns. The survey in year 4 will provide an important secondary endpoint evaluating the effect of the alternative schedule in the population as children receiving the alternative schedule age and accumulate within the population.

In order to isolate the herd effects of the schedules in very young infants, the secondary endpoint of VT carriage prevalence in infants aged 6–12 weeks presenting for their first dose of PCV13 will be measured in a cross-sectional manner in year 4 (Fig. 3). Safety endpoints covering the incidence of clinical pneumonia, radiological pneumonia, IPD, hospitalisation and mortality will be measured throughout the 4 years of the trial (Fig. 3). The incidence of clinical pneumonia associated with NP carriage of VT and NVT pneumococci will also be measured.

The dynamics of age-dependent VT pneumococcal transmission are complex and vary by population, contact patterns and the related carriage data have important implications on accurate vaccine protection estimates [39, 40]. Including an interpersonal contact pattern survey in Year 2 parallel with the survey of VT carriage will generate data on contact patterns for planned mathematical modelling of the effect of alternative PCV schedules. The parallel surveys will give insight into the magnitude of association between age-related carriage prevalence and rates of interpersonal contact and whether infection is associated with physical or non-physical contacts.

The emergence of NVT serotypes causing IPD in both children and adults following the introduction of PCV13 has been a source of concern. The effect of an alternative schedule on serotype replacement dynamics has not been well described. The measurement of NVT pneumococcal carriage in the population in years 2 and 4 will provide data on the effect of the alternative schedule on NVT pneumococcal transmission

### Participant timeline {13}

Participants in the trial are enrolled in one of the two groups (Table 1, Fig. 3) with the timing of specimen enrolment, interventions, and assessments shown in Fig. 4.

**Fig. 4 Fig4:**
[figure not shown]
Adapted SPIRIT figure showing the timeline of cluster allocation, enrolment, intervention, and assessments for infants enrolled at EPI clinics. PCV13 (PCV) – 13 valent pneumococcal conjugate vaccine; 3 + 0 – standard schedule of three primary doses; 1 + 1 – alternative schedule of one primary dose and one booster dose. *VT* vaccine-type pneumococcal serotype. *Clinical presentations to health facilities and vital status are under continuous surveillance among infants enrolled at EPI clinics to receive the interventions and among all resident children < 5 years of age

### Non-inferiority margin

We determined the non-inferiority margin using the concept of ‘the largest loss of impact of the current treatment that would be clinically acceptable’, an approach recommended by the US FDA [41]. The non-inferiority margin uses a relative metric as the relative effect of the standard schedule is likely to be constant. The introduction of the 3 + 0 schedule has reduced NP VT prevalence in children from 47 to 13%, i.e. a 72% reduction (author’s own data). Baseline risk may change over time, so an absolute value for the non-inferiority margin may not provide a reliable measure of the difference in impact of the two schedules.

Given the important advantages of the 1 + 1 schedule, the non-inferiority margin will be a 15% loss of the impact of the 3 + 0 schedule; this value is supported by empiric survey data. An online survey was sent to 72 individuals involved in pneumococcal vaccine research, policy and clinical care. Valid responses were received from 19 respondents. The survey question presented 10 hypothetical results of VT prevalence in the two trial groups, on a scale of increasing ‘loss of impact’ associated with the 1 + 1 schedule, from a baseline of no loss (i.e. a 0% loss of impact) in the 1 + 1 versus 3 + 0 group, up to a 50% loss of impact. Respondents were asked to consider themselves as decision-makers in their national immunisation programmes requested to consider a change to their national programme from a 3 + 0 to 1+ 1 schedule based on the results of the trial. Respondents selected one option corresponding to the ‘loss of impact’ which would sway their decision against introducing the new 1+ 1 schedule. Using the metric of a percentage loss of impact of the 3 + 0 schedule which would sway decisions against the new schedule the mean value was a 22% loss of impact. The results of the survey support our decision to use a non-inferiority margin that the 1 + 1 schedule be associated with a ≤15% loss of the total impact of the 3 + 0 schedule.

The prevalence of NP carriage of VT pneumococci from Jan–Sept 2015 was 17% and fell to 15% in Oct–Dec 2015 (author’s own data). Assuming VT prevalence of 13% in the 3 + 0 group at the beginning of the trial, a 15% loss of impact translates to prevalence in the 1+ 1 group of (1 − [0.72 − (0.72 × 0.15)]) × 47% = 18.3%. We used changes in VT prevalence to inform the non-inferiority margin because reductions in VT carriage following the introduction of PCV can predict the impact of PCV on IPD and because carriage prevalence is proportional to the rate of pneumococcal transmission in the population [42].

For the secondary endpoints of community pneumococcal carriage, the non-inferiority margin of a ≤15% loss of impact in the 1+ 1 compared to the 3+ 0 schedule clusters, will be used as described above. The same VT prevalence will be assumed within the community.

### Sample size {14}

Sample size calculations were based on the primary outcome of NP carriage of VT pneumococci in children aged 2 weeks–59 months with clinical pneumonia. The primary outcome will be measured in random samples of participants in each of the 68 clusters (if a minimum of 60 participants were sampled in each cluster there would be 1980 in each arm and 3690 in total). Using Basse data from 2015, we assumed that the prevalence of VT carriage to be 13% in both the 3 + 0 and 1 + 1 arms. Based on the non-inferiority assumptions presented in the previous section, the 1 + 1 schedule will be considered non-inferior if the upper limit of the one-sided 95% confidence interval for the prevalence ratio is ≤1.38 (0.18/0.13 = 1.38). Using Basse data, we estimated the intra-class correlation (ICC) to be 0.01–0.02. We calculated study power using the methods of Farrington et al. [43] and Donner et al. [44]. Using the more conservative value for ICC of 0.02, a minimum number measured for the endpoint per cluster of 60, 33, and 35 clusters per arm (with design effect of 2.18) and alpha=0.05, a sample size of 1980 per arm will provide 93% power to test the non-inferiority of the 1 + 1 schedule.

To increase confidence in the power of the study we simulated trial data using 2015 data from the BHDSS based on cluster-wise VT carriage in children with pneumonia. The simulated data were designed to be similar to the villages included in this trial with respect to the mean carriage prevalence, as well as the variability in prevalence across clusters. Using 1000 simulated populations, each consisting of 68 clusters of 60 individuals, baseline prevalence of 10% and a largest acceptable increase of 4%, i.e. from 10 to 14%, study power was ≥85% in most scenarios.

As opposed to the non-inferiority hypothesis that is specified in year 4 of the study we will specify a superiority hypothesis for the measurement in year 2 of VT prevalence in children with clinical pneumonia. Setting a 5% level of significance and power of 80%, with ICC=0.02 and assuming the prevalence of VT carriage in the control group is 18%, we wish to detect an absolute difference of 8%. That is, the smallest clinically significant difference that we wish to detect is equivalent to 18% versus 26% prevalence in the two groups. Given these parameters, if we measure the endpoint in 20 individuals per cluster, we would need to include 29 clusters in each group, that is, a total of 58 clusters. We will measure the endpoint in 68 clusters.

Study power for the secondary endpoint of VT prevalence in infants aged 6–12 weeks presenting for their first dose of PCV is based on the same assumptions as for the primary endpoint and study power will be similar to that for the primary endpoint.

In the community carriage surveys in years 2 and 4, we will sample 60 residents in each of the 68 clusters. The same assumptions and methods of power calculation as for the primary endpoint were used. We assume ICC=0.02, 15% baseline VT carriage prevalence in both clusters, and a ≤1.38 prevalence ratio derived from the ≤15% NI margin. If the upper bound of the 95% confidence interval of our prevalence ratio comparing the 1 + 1 to the 3+ 0 clusters is ≤1.38, then the alternative schedule will be considered non-inferior. Following these assumptions, the community carriage surveys in years 2 and 4 will have power > 94% if we collect 4080 samples evenly across 68 clusters (i.e. 60 per cluster).

For the interpersonal-contact pattern survey in year 2, 1500 participants from the carriage study will be enrolled. Recruiting 1500 participants will enable us to detect an absolute difference of 1 mean contact per day between age groups, with a 5% significance level, and 90% power. These calculations are based on the work of le Polain de Waroux et al. [45]. The study is not powered to determine non-inferiority for other secondary or safety endpoints.

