## Statistical methods

### Statistical methods for primary and secondary outcomes {20a}

Coverage of each schedule during the course of the trial will be reported at the end of each of the four annual periods, as the proportion of surviving, resident children, who have completed the respective schedules at the ages of 12 and 18 months. Coverage calculations will be classified as receiving the respective schedules in a timely (completed before age 7 months [3 + 0] or 13 months [1 + 1]) or delayed fashion. Cross-over between groups will be defined as (a) change of residential location from a 1 + 1 to 3 + 0 cluster, and vice versa, for a period of 4 or more months and (b) receipt of the third dose of PCV at 8 months of age or greater in a 3 + 0 cluster.

The unit of inference will be the individual child. That is, we wish to estimate whether the risk of VT carriage in a child who lives in a geographic area using a 1 + 1 schedule is not greater than the given threshold when compared to a child in an area receiving the 3 + 0 schedule. The primary outcome will be presented as the proportion (prevalence) of children with clinical pneumonia and NP carriage of VT pneumococci. The contrast between the two groups will be presented as a prevalence ratio (and 95% confidence intervals), with ratios expressed as the prevalence in the 1+ 1 group compared to the prevalence in the 3 + 0 group. To account for cluster-level non-independence, the primary analysis will use generalised estimating equations (GEE) with a log link, binomial family and exchangeable correlation structure. The GEE models will adjust for stratification variables, and age will be included in the model for the endpoint of VT carriage in unimmunised infants aged 6-12 weeks, due to rapid age-related changes in prevalence in the first months of life. Non-inferiority will be established if the upper limit of the confidence interval around the prevalence ratio is ≤1.38.

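### The non-inferiority rule uses a one-sided 95% limit where the trial is sized but an unqualified 95% interval in the analysis text and for the community surveys, and nothing reconciles the two

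*Protocol article*

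**What the plan says.** **Sample size {14}, primary endpoint.** Non-inferiority holds if "the upper limit of the one-sided 95% confidence interval for the prevalence ratio is ≤1.38". The power statement uses "per cluster of 60, 33, and 35 clusters per arm (with design effect of 2.18) and alpha=0.05" and concludes that "a sample size of 1980 per arm will provide 93% power to test the non-inferiority of the 1 + 1 schedule".

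**Sample size {14}, community surveys.** The rule begins "If the upper bound of the 95% confidence interval of our prevalence ratio" and applies the same 1.38 limit. The word one-sided is absent, although this is the same section and the methods are said to be those of the primary endpoint.

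**Statistical methods {20a}, primary endpoint.** "The contrast between the two groups will be presented as a prevalence ratio (and 95% confidence intervals"), and then: "Non-inferiority will be established if the upper limit of the confidence interval around the prevalence ratio is ≤1.38". The decision sentence gives neither a level nor a side. The only interval named before it in that paragraph is the 95% interval used for presentation.

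**Statistical methods {20a}, secondary carriage endpoints.** The same pattern recurs: 95% intervals for presentation, then an unqualified upper limit compared with 1.38. The section also gives the year 2 superiority analysis an alpha of 0.05 and says the final analysis will use the same value, without stating a side.

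One-sided appears once in the article. Two-sided and 0.025 do not appear.

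**The concern.** A non-inferiority claim depends on one limit of one interval. The one-sided 95% upper limit equals the upper limit of a two-sided 90% interval and carries a 5% false-positive rate at the margin. The upper limit of a conventional 95% interval carries 2.5%. If the sizing text and the analysis text point to different limits, the same data can pass one and fail the other, and the stated power belongs to only one of them. This is the primary success criterion of a trial meant to inform vaccine policy, so the criterion should read the same way wherever it appears.

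**Working it through.** **Inputs (Sample size {14}).** "we assumed that the prevalence of VT carriage to be 13% in both the 3 + 0 and 1 + 1 arms"; 60 per cluster; 1980 per arm; margin 1.38. "Using the more conservative value for ICC of 0.02" gives a design effect of 1 + 59 × 0.02 = 2.18. Effective size per arm is 1980/2.18 = 908.3. All calculations use normal approximations, with no small-sample correction for the number of clusters.

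**1. Reproduce the stated 93%.** On the difference scale the margin is 0.13 × 0.38 = 0.0494, or 0.05 from 0.18 − 0.13.
- SE = √(2 × 0.13 × 0.87 / 908.3) = 0.01578.
- Power = Φ(margin/SE − z), where margin/SE is 3.130 or 3.168.
- One-sided 0.05 (z = 1.645): 93.1% to 93.6%. This reproduces 93%.
- One-sided 0.025 (z = 1.960): 87.9% to 88.7%. This does not.

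**2. Same inputs on the log-ratio scale, the scale of the planned log-link GEE.**
- SE = √(2 × (0.87/0.13) / 908.3) = 0.1214.
- ln 1.38 / SE = 0.3221/0.1214 = 2.653.
- Power is 84.3% at one-sided 0.05 and 75.6% at 0.025.
- With 33 and 35 clusters (1980 and 2100 children), SE = 0.1196 and the powers are 85% and 77%.

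Only the drop within a scale is due to sidedness: about 5 points on the difference scale and 8 to 9 on the log-ratio scale. The gap between 93% and 84–85%, both at one-sided 0.05, comes from the scale.

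**3. Where the verdicts diverge.** The largest observed ratio that passes is 1.38 × exp(−z × SE).

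| Rule | SE 0.1214 | SE 0.1196 |
|---|---|---|
| One-sided 95% | 1.130 | 1.134 |
| Two-sided 95% | 1.088 | 1.092 |

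At SE 0.1214, the chance of an observed ratio between the two limits is 8.7% if the true ratio is 1.0, 12.5% if it is 1.1 and 10.1% if it is 1.2.

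**4. Community surveys.** Prevalence is 15%, with 2040 per arm (4080/2) and design effect 2.18, so effective size is 935.8 per arm. The difference-scale margin is 0.15 × 0.38 = 0.057, SE = √(2 × 0.15 × 0.85 / 935.8) = 0.01651, and margin/SE = 3.453. Power is 96.5% at one-sided 0.05 and 93.2% at 0.025. The stated figure is above 94%, so only the first meets it.

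**5. Does the alpha of 0.05 in {20a} settle the matter?** That sentence ties the final analysis to the alpha of the year 2 superiority test. The year 2 sizing is 18% against 26%, 20 per cluster, ICC 0.02 and 80% power. At two-sided 0.05 it needs 420 per group before inflation; 420 × 1.38/20 = 28.98, the stated 29 clusters. (Here 1.38 is the design effect, 1 + 19 × 0.02.) At one-sided 0.05 it needs 331, and 331 × 1.38/20 = 22.8, or 23 clusters. The shared alpha was therefore two-sided in the year 2 sizing, and the sentence does not show which side applies to the final analysis.

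**6. Sensitivity.** Steps 1 and 4 use the stated limit of 1.38. The non-inferiority margin section derives 18.3% before rounding, a ratio of 18.3/13 = 1.408 and a difference of 0.053. With that wider margin, difference-scale primary power at one-sided 0.025 is 91.9% (1980 per arm) to 92.6% (33 and 35 clusters). Community power, with 0.15 × 0.408 = 0.0612, is 95.9%. The inference from power to intended rule therefore depends on the 1.38 that the decision rule states.

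**The case against.** The strongest reply is that the article has one complete rule and several looser repeats. The sample size section fixes side, level and margin. The later sentences repeat the margin and omit the rest, which is an omission and not a competing rule. The community-survey power is said to use the primary endpoint's methods, and {20a} says the secondary endpoints use the primary endpoint's non-inferiority measurement. Both links favour carrying the one-sided rule over, and at the stated margin so do the stated powers.

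Much of this stands. One-sided 0.05 is the likelier intention. But no sentence carries the rule into {20a}, the qualifier is dropped even within the sample size section, and an unqualified 95% interval is ordinarily read as two-sided.

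Three stronger readings are tempting and are not supported:
- **That the analysis section prescribes a two-sided test at 0.025.** It states neither. That is how the wording would usually be read, not what it says.
- **That the verdict can be chosen once the data are seen.** The article requires the Trial Steering Committee to approve a statistical analysis plan, which is not shown here and may fix the level. Statisticians are also to work with masked group labels.
- **That sidedness takes power from 93% to about 77%.** That adds the scale gap to the sidedness effect. On the scale that reproduces 93%, sidedness takes it to about 88%.

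**Conclusion.** The point holds as an unreconciled statement of the primary decision rule: explicit one-sided 95% in one place, an unqualified 95% interval elsewhere. Under the two readings the false-positive rate at the margin is 5% or 2.5%, and an observed ratio of about 1.09 to 1.13 changes verdict. Primary power is about 93% or 88% on the difference scale, and 84–85% or 76–77% on the log-ratio scale. Community-survey power is 96.5% or 93.2% on the difference scale.

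These figures assume the planning prevalences, an ICC of 0.02, 60 per cluster and the 1.38 margin. A different ICC or prevalence in year 4 would move the 1.09–1.13 window without removing it. The shortfall of ratio-scale power below 93% at one-sided 0.05 is a separate matter.

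**What to change.** Before the year 4 analysis, write one rule in the same words for the primary endpoint and the community surveys in Sample size {14}, and for the primary and secondary carriage endpoints in {20a}. The statistical analysis plan should carry the same words.

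- **To match the sizing:** judge non-inferiority on the upper limit of the one-sided 95% interval (equivalently, the two-sided 90% interval) against 1.38. Say that the two-sided 95% interval is reported for estimation only.
- **If the two-sided 95% limit is preferred:** use it throughout and restate primary and community power at one-sided 0.025, naming the scale. Primary power is then about 88% on the difference scale, or 76–77% on the log-ratio scale of the planned GEE. Community power is about 93% on the difference scale, or 83% on the log-ratio scale (SE 0.1101; 0.3221/0.1101 − 1.960 = 0.967).

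In either case, state the side of the alpha for the final analysis separately from that of the year 2 superiority test. The cost is wording and, for the second option, a restated power paragraph. No data collection changes.
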